#### Masking

Masking of participants and therapists is not possible due to the nature of the intervention. However, the principal investigator and the research assistants are masked until after the primary outcomes of the study are analysed.

#### Measurements

In total seven measurements take place. One at baseline and thereafter at every step of the intervention (at 3, 6, 9 and 12 months) and at follow-up (at 18 and 24 months). Outcome measures are obtained over the phone by masked research assistants. These assistants are trained (by the first author) to follow a predetermined protocol. The first interview takes approximately 45 minutes; the next interviews take approximately 30 minutes. In Figure 2 an overview of the design is presented.

**Figure 2 F2:**
[figure not shown]
Overview of the RCT design.

#### Outcomes

The primary outcome of this study is the incidence of depressive (major depression and dysthymia) or anxiety disorders (panic disorder, agoraphobia, social phobia and generalised anxiety disorder) as measured with the Mini International Neuropsychiatric Interview (MINI) [47], using the electronic version MiniManager 2.0 (de Beurs, Leiden University Medical Centre). Secondary outcome measures are subthreshold depression measured with the Centre for Epidemiologic Studies Depression scale (CES-D) [37,38] and subthreshold anxiety measured with the Hospital Anxiety and Depression Scale – Anxiety (HADS-A) [39]. Other secondary outcome measures are vision related quality of life as measured with the Low Vision Quality Of Life questionnaire (LVQOL) [49,50] and health related quality of life measured with the EuroQol-5 Dimensions (EQ-5D) [51]. Adaptation to vision loss is measured with the Adaptation to age-related Vision Loss (AVL) questionnaire [52] and perceived need for care is measured with the Perceived Need for Care Questionnaire (PNCQ) [53]. For the process-evaluation the Dutch Mental Healthcare Thermometer (DMH thermometer) is used to evaluate the different steps of the stepped-care programme [54]. For the cost-evaluation the Trimbos/iMTA questionnaire for Costs associated with Psychiatric illness (TicP) is used to measure health care utilisation [55] and the Short Form Health and Labour Questionnaire (SF-HLQ) to measure absenteeism and presenteeism from paid and unpaid work [56]. Standard costs for health care utilization from the Dutch costing guidelines are used [57]. Medication use is valued using prices of the Royal Dutch Society of Pharmacy. Productivity losses will be valued using the Friction Cost Approach. In Table 1 the different outcome measures are presented per follow-up measurement.

**Table 1 T1:** Outcome measures, instruments and assessments

**Steps**	**T0**	**T1**	**T2**	**T3**	**T4**	**T5**	**T6**
		**3 m**	**6 m**	**9 m**	**12 m**	**18 m**	**24 m**
**Primary Outcome**							
Depression or anxiety disorder (MINI) [47]	x	x	x	x	x	x	x
**Secondary Outcomes**							
Subthreshold depression (CES-D) [37,38]	x	x	x	x	x	x	x
Subthreshold anxiety (HADS-A) [39]	x	x	x	x	x	x	x
Six item screener [48]	x						
Vision related quality of life (LVQOL) [49,50]	x				x		x
Health related quality of life (EQ5D) [51]	x				x		x
Adaptation to age-related Vision Loss (AVL) [52]	x				x		x
Perceived need for care (PCNQ) [53]	x	x	x	x	x	x	x
Patient satisfaction (DMH thermometer) [54]		x	x	x	x		
Health care utilisation (Tic-P) [55]	x		x		x		x
Health and labour (SFHLQ) [56]	x		x		x		x

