Some studies have shown that interventions aimed at preventing major depression and/or reducing subthreshold symptoms of depression in the visually impaired can be effective. Horowitz et al. (2005) found that variable low vision rehabilitation services, such as counselling and use of optical devices had a small positive effect on the decline of depressive symptoms after two years [5,19]. In another trial, with a follow-up period of six months, Horowitz et al. (2006) showed that optical devices that optimise residual vision, as apposed to adaptive aids that involve learning new methods to compensate for lost functions, had a positive effect on the course of depressive symptoms [20]. Brody et al. (2006) found that a self-management programme consisting of cognitive and behavioural elements including health education and enhancement of problem-solving skills, significantly reduced depressive symptoms in people with age-related macular degeneration (AMD) after six months [21]. Rees et al. (2007) concluded that self-management programmes for visually impaired adults are a promising way to help address emotional distress [22]. Girdler et al. (2010) also evaluated a self-management programme in visually impaired older adults and reported significantly less depressive symptoms at 12 weeks in participants who received the programme as apposed to patients who received standard visual rehabilitation services [23]. Rovner and Casten (2008) found that problem solving treatment (PST), a short behavioural treatment in which participants learn a new method to address problems that interfere with everyday functioning, prevented the onset of depressive disorders in elderly with AMD after two months. However, after six months there was no statistically significant difference in depressive disorders between the intervention- and control group [24]. To prevent the onset of depression on the long term Rovner and Casten (2008) suggest to either continue treatment in this high risk group after providing PST or focus on preventive treatment for patients that show early signs of depression [24]. Currently, Rovner and colleagues are performing the Improving Function in Age-related Macular Degeneration study (IF-AMD) in which they are investigating the efficacy of PST compared to Supportive Therapy in preventing depressive disorders [25]. Margrain and colleagues are currently performing the Depression in Visual Impairment Trial (DEPVIT) to reduce depressive symptoms in visually impaired adults. They are comparing three groups: one group that receives PST with additional self-help materials, one group that is referred to the general practitioner (GP) and one ‘waiting list control’ group [26].

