#### Final protocol

Figure 1 shows the final stepped-care programme, which consists of four consecutive steps. Each step takes approximately three months. Only if symptoms of depression and/or anxiety persist, then patients move on to the next step. Severity of symptoms is measured with the Epidemiologic Studies Depression scale (CES-D) [37,38] and the Hospital Anxiety and Depression Scale – Anxiety (HADS-A) [39]. Only if patients have a score of 16 or higher on the CES-D and/or a score of 7 or higher on the HADS-A, then they move on to the next step.

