#### Statistical analysis

The analyses are based on the intention-to-treat principle. Statistical analyses are performed using SPSS 20. First, descriptive statistics of baseline characteristics are compared to check whether randomisation is successful in generating two similar groups. Survival analyses and mixed modelling is then used to compare the treatment and control group. All available data in all measurement cycles are used to estimate the longitudinal trial outcomes at 3, 6, 9, 12, 18 and 24 months after baseline.

For the economic evaluation multiple imputation is used to impute missing data. Bias-corrected and accelerated bootstrapping with 5000 replications is used to estimate 95% confidence intervals around the mean difference in total costs between the treatment and control group. Incremental cost-effectiveness ratios (ICERs) are calculated. Bootstrapping is used to estimate the uncertainty surrounding the ICERs. Cost-effectiveness acceptability curves and net monetary benefits are also estimated.

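### Year-two costs rest on one questionnaire at 24 months, and EQ-5D at 0, 12 and 24 months cannot show utility changes within a year, although 6- and 18-month interviews already take place

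*Protocol article*

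**What the plan says.** Cost-effectiveness is a stated aim of the trial (Background; Design of a randomised controlled trial). The Statistical analysis section plans to estimate the "mean difference in total costs between the treatment and control group", with ICERs, acceptability curves and net monetary benefits. Missing economic data are to be multiply imputed.

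The Measurements section sets interviews at baseline, 3, 6, 9, 12, 18 and 24 months. Table 1 then marks:

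- "Health care utilisation (Tic-P) [55" (TiC-P) and "Health and labour (SFHLQ) [56" (SF-HLQ) at 0, 6, 12 and 24 months, with nothing at 18;
- "Health related quality of life (EQ5D) [51" at 0, 12 and 24 months, with nothing at 3, 6, 9 or 18;
- MINI, CES-D, HADS-A and the perceived-need questionnaire at all seven points, including 18 months.

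On the timing of treatment, the Final protocol section says "Each step takes approximately three months", and there are four steps. The article does not give the recall period of either cost questionnaire, the time horizon of the economic evaluation, or the effect unit of the ICER.

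**The concern.** In year one the cost questionnaires are 6 months apart. In year two there is only one, 12 months after the last. Either its recall window is shorter than 12 months and part of year two is unobserved, or it relies on a 12-month look-back that no year-one questionnaire needs. Multiple imputation does not repair this: it can fill an answer that some participants gave, but an assessment scheduled for nobody supplies no observed values to model.

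The uncovered months need not cost the same in both arms. With steps of about three months, GP referral begins around month 9, so care that follows from it can fall after month 12. Recovered patients whose symptoms return can start the following step later. Controls are expected to have more disorders (40% against 20% over two years, Sample size), which also generates care. The error in the cost difference could go either way.

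For utilities, nothing is measured between baseline and month 12, which is when steps 2–4 run. A short-lived benefit is conceivable: the Background cites a problem-solving trial in macular degeneration with an effect at two months, where "after six months there was no statistically significant difference in depressive disorders between the intervention- and control group".

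**Working it through.** The article gives no figure on this point to reproduce. The inputs are the Table 1 schedule, plus assumed recall periods and assumed utility gains, labelled as such.

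**Costs.** A questionnaire at month *t* with recall *r* covers months *t − r* to *t*. Baseline recall falls before randomisation and adds nothing. In months 12–24, one questionnaire at 24 leaves 12 − *r* months uncovered. Adding one at 18 leaves 12 − 2*r* (not below 0). Over the full 24 months the present schedule leaves 24 − 3*r* for *r* up to 6.

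| Assumed recall (months) | Uncovered in 12–24, now | Uncovered in 12–24, with 18-month call | Uncovered in 0–24, now |
|---|---|---|---|
| 1 | 11 | 10 | 21 |
| 3 | 9 | 6 | 15 |
| 6 | 6 | 0 | 6 |
| 12 | 0 | 0 | 0 |

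With 6-month recall, months 12–18 are missing: 6/24 = 25% of follow-up and half of year two. With recall below 6 months, parts of year one are uncovered as well.

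**Utilities, if QALYs are used.** The QALY difference is the trapezoid sum of (t₂ − t₁)/12 × (u₁ + u₂)/2, where *u* is the between-arm utility difference. The illustrative peak gain is 0.05. In the first three rows it rises linearly from 0 at month 3 to 0.05 at month 6.

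| Assumed course | True | EQ-5D at 0/12/24 | EQ-5D at 0/6/12/18/24 |
|---|---|---|---|
| Sustained to 24 | 0.0813 | 0.0750 (-8%) | 0.0875 (+8%) |
| Held to 9, 0.025 at 12, zero at 24 | 0.0406 | 0.0250 (-38%) | 0.0438 (+8%) |
| Held to 9, zero at 12 | 0.0250 | 0 (-100%) | 0.0250 (0%) |
| Starts after 9, full at 12, sustained | 0.0563 | 0.0750 (+33%) | 0.0625 (+11%) |
| Linear to 12, then held | 0.0750 | 0.0750 (0%) | 0.0750 (0%) |

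Worked for the first row:
- True: 0.25 × 0.025 + 1.5 × 0.05 = 0.00625 + 0.075 = 0.0813.
- Yearly grid: 1 × 0.025 + 1 × 0.05 = 0.0750.
- Six-monthly grid: 0.5 × 0.025 + 1.5 × 0.05 = 0.0875.

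For the third row:
- True: 0.00625 + 0.0125 + 0.00625 = 0.025.
- Yearly grid: 0, because the difference is zero at all three points.

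Doubling the assumed gain to 0.10 doubles every QALY figure and leaves the percentages unchanged.

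**The case against.** A reader might infer that the schedule leaves a 12-month hole in the cost data. It does not: 12 months is the spacing between questionnaires. The uncovered part of year two is 0 to 11 months over the recalls tried, and recall is a detail an article may leave to the full protocol. If recall is read from the spacing, the 24-month questionnaire would look back 12 months and the problem would be long recall alone.

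A reader might also take a 24-month economic horizon and QALYs as given. Both are inference. The questionnaires run to 24 months and EQ-5D is collected, but the article names neither. An ICER per disorder prevented would use the MINI, collected at all seven points, and would escape the utility problem, though not the cost problem.

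Nor is the EQ-5D blind to treatment altogether: four steps of about three months end near month 12, when it is measured. What is missing is any utility between baseline and that point.

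The case for a transient effect is also one-sided. The cited trial tested problem-solving treatment alone, with disorder onset as its outcome. The stepped-care trial behind the sample size is reported as holding its effect at 24 months (Evidence from previous studies). In that sustained case the denser grid exchanges -8% for +8%, which is no gain in accuracy.

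Finally, the Challenges section warns that the amount of questioning may raise drop-out, so the lighter calls may be deliberate.

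All of this stands and narrows the point. It does not remove the reliance on one questionnaire for year-two costs, nor the lack of protection against an effect that changes within a year.

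**Conclusion.** The point holds in limited form, for the economic evaluation only. Year-two costs come from one questionnaire and are either incomplete (11, 9 or 6 of 12 months uncovered at assumed recalls of 1, 3 or 6 months) or dependent on 12-month recall, out of line with year one. This matters to the extent that the evaluation extends beyond month 12.

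The utility part is conditional on QALYs being the effect measure. Its size depends on the course of the effect: negligible to -8% for an early or gradual sustained gain, -38% to -100% for the two fading courses tried, and an overstatement of a third for late onset. These percentages come from illustrative curves and are not predictions. The documents do not support a claim that the cost-effectiveness result will be wrong by a stated amount. The primary outcome and its analysis are unaffected. This is an inexpensive improvement to the schedule.

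**What to change.** Add TiC-P and SF-HLQ to the existing 18-month interview, and EQ-5D to the existing 6- and 18-month interviews, so that costs and utilities share one 6-monthly grid. This closes the year-two cost gap fully if recall is at least 6 months. With 3-month recall, 6 months of year two would remain uncovered, so the recall window should be checked against the spacing.

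Estimate the cost and utility differences adjusted for baseline costs and baseline EQ-5D. Both are already collected, so this adds no data burden.

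For participants already past a visit, EQ-5D values imputed from that visit's CES-D and HADS-A scores are suitable only for a sensitivity analysis.

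The cost is a small amendment and somewhat longer interviews at two calls that take place anyway. The later interviews are put at about 30 minutes, in a frail population where question burden is already named as a drop-out risk. If that burden has to be limited, the 18-month cost questionnaires come first, because the cost problem does not depend on which effect measure is chosen.

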#### Sample size

The power calculation is based on the study of van Van ‘t Veer et al. 2009 in which a comparable stepped-care programme was tested in older adults [32]. Results form this study showed that over a period of two years approximately 40% of older adults in the control group, which was not depressed at baseline, became depressed during this study, versus 20% of older adults in the intervention group. Therefore, it is expected that the programme will lead to a reduction of depressive and anxiety disorders of 50% (approximately 20% versus 40%). Based on a power of 85%, a significance level of 0.05 (two-sided) and a drop-out rate of 20%, 115 patients are needed in each group to demonstrate an effect size of 0.50. Approximately 3000 visually impaired patients (of 50 years and older) of one of the rehabilitation organisations, are invited to participate in the screening for this study. We expect that approximately 30% is willing to cooperate, resulting in 900 patients who can be screened for symptoms of depression and anxiety with the CES-D and HADS-A and on depressive or anxiety disorders with the MINI, by means of a telephone interview. This will result in approximately 230 eligible patients.

#### Statistical analysis

The analyses are based on the intention-to-treat principle. Statistical analyses are performed using SPSS 20. First, descriptive statistics of baseline characteristics are compared to check whether randomisation is successful in generating two similar groups. Survival analyses and mixed modelling is then used to compare the treatment and control group. All available data in all measurement cycles are used to estimate the longitudinal trial outcomes at 3, 6, 9, 12, 18 and 24 months after baseline.

For the economic evaluation multiple imputation is used to impute missing data. Bias-corrected and accelerated bootstrapping with 5000 replications is used to estimate 95% confidence intervals around the mean difference in total costs between the treatment and control group. Incremental cost-effectiveness ratios (ICERs) are calculated. Bootstrapping is used to estimate the uncertainty surrounding the ICERs. Cost-effectiveness acceptability curves and net monetary benefits are also estimated.

## Discussion

Depression and anxiety symptoms are common in visually impaired older adults and this elderly group will only grow in the future because of the ageing of the population. It is crucial to treat depressive and anxiety symptoms, because they are the most important predictors of developing a full-blown depressive or anxiety disorder. However, the evidence for preventive interventions has received little attention in the field of low vision. This study aims to investigate an indicated preventive intervention to prevent the onset of depressive and anxiety disorders in patients that show early signs of the disorders.

### Strengths

This study is innovative because the (cost-)effectiveness of a stepped-care programme to prevent depression and anxiety has never been tested in a visually impaired population before. Additionally, the programme is based on successful stepped-care interventions for older adults in the general population [31-33] and other effective components of preventive interventions in the field of low vision [21,24]. Another strength of this study is that the treatment is aimed at preventing both depression and anxiety. The few studies, that investigated interventions to reduce depression in the field of low vision, did not take anxiety into account while several other studies suggest that anxiety is as important a problem for visually impaired older adults as depression is [58,59]. Moreover, this stepped-care programme is embedded within rehabilitation organisations for the visually impaired, where health care workers with the specific expertise of working with visually impaired older adults can offer treatment to reduce symptoms of depression and anxiety in addition to usual visual rehabilitation care. It is very important to address depression and anxiety in this setting because depression and anxiety seriously complicate successful rehabilitation. By letting healthcare workers from the rehabilitation organisations provide the treatment themselves, continuation of the intervention after the end of this trial is highly improved. This pragmatic design enhances the generalisability of this study.

### Challenges

The recruitment of participants is likely to be difficult because it is a challenging subject for a very frail population (older adults, visually impaired and symptoms of depression and/or anxiety). To address this challenge and to allow patients to receive oral information about the study, all patients (approximately N = 3000) who receive written patient information on the study are approached by telephone by the rehabilitation organisations. Still, drop-out rates may be high because of the vulnerability of the population (sickness, death) and because of the quantity and types of questions that are asked. The way in which these questions are asked may be confronting and cause feelings of sadness or worry. Patients might also have low motivation to comply to the different steps of the programme, because of their depressive state [60]. Therapist support will be used to stimulate their motivation [45]. Another challenge is the possibility of contamination: health care workers might give more attention to problems of depression and anxiety because of their newly learned skills to provide support for these problems to patients outside the intervention group. Therefore, it is stressed to health care workers to not offer treatment according to the stepped-care programme to patients outside the intervention group. Finally, it may be difficult to weigh the specific contributions of the various steps in the stepped-care programme, because of the pragmatic design of the study. Not all patients of the intervention group follow the same steps of the programme.

## Conclusion

The importance and strengths of this study outweigh the challenges. The development and research of the (cost-)effectiveness of a stepped-care programme to prevent depressive and anxiety disorders in visually impaired older adults is of the greatest importance.

## Abbreviations

AMD: Age-related macular degeneration; PST: Problem solving treatment; GP: General practitioner; RCT: Randomised controlled trial; CBT: Cognitive behavioural therapy.
